### Ethics approval

3.2

This trial protocol has been approved by the Ethics Committee of the Affiliated Hospital of Chengdu University of Traditional Chinese Medicine (2023KL-063), and registered in https://ClinicalTrial.gov (Identifier: ChiCTR2300076182). The study is performed according to the Helsinki Declaration. Permission will be obtained from hospital before conducting. The Ethics Committee will supervise and review the design and implementation of the trial methods.

### Sample size calculation

3.3

According to a prior clinical study (32), sample size estimation is based on the Montreal Cognitive Assessment (MoCA) score. The differences in MoCA scores before and after treatment was (3.22 ± 1.88) for the acupuncture group and (1.97 ± 1.77) for the placebo acupuncture group. In the formula, with *α* = 0.05, *β* = 0.10, and k = 1, a sample size of 37 cases per group was calculated. Considering a dropout rate of 20%, we determined a sample size of 45 cases per group. Consequently, the total number of cases in both groups will be 90.

Using brain imaging data as an indicator of acupuncture-related studies, the sample typically ranged from 10 to 25 individuals per group (33–35). Thus, we will enroll at least 20 participants per group in fNIRS scanning. Considering a dropout rate of 20%, we determined a sample size of 24 cases per group.
$$n=\frac{{\left(u_{\alpha }+\mu_{\beta }\right)}^{2}\left(1+1∕k\right)\sigma^{2}}{\delta^{2}}$$

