### Randomization and blinding

3.10

Participants will be randomly assigned to two groups in a 1:1 ratio using computer-generated random numbers. During intervention phase, participants will be administered separately in quiet treatment rooms to prevent interactions from different groups. Throughout the study, researchers, acupuncturist, efficacy assessors, and data statisticians will remain segregated. Only the acupuncturist aware of the group assignment result. Participants, evaluators, and analysts will be blinded to group assignments.

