## Data analysis

7

Data analysis will follow the intention-to-treat (ITT) strategy and will be conducted using IBM SPSS version 26.0 software (IBM Corp, New York). A *p*-value of ≤0.05 will be considered statistically significant. To address missing data, the Last Observation Carried Forward (LOCF) method will be employed for imputation. Continuous variables will be expressed as mean ± standard deviation, while categorical variables will be presented as numbers and percentages. Categorical variables will be analyzed using the Chi-Square Test. For continuous variables that follow a normal distribution, comparisons between groups will be made using an independent samples *t*-test, while paired samples *t*-tests will be used for pre- and post-treatment comparisons within the same group. For continuous data that do not follow a normal distribution, the Mann–Whitney U test will be used, with results expressed as the median and interquartile range. *p*-values obtained from the statistical tests, both for clinical outcomes and fNIRS data, will be corrected using the false discovery rate (FDR) method to account for multiple comparisons.

The raw fNIRS data will be preprocessed using NIRSPARK software, which includes format conversion, motion correction, artifact processing, and bandpass filtering. Data analysis will be performed using a dedicated module in MATLAB (R2020a).

Previous studies have demonstrated that patients with cognitive impairment due to insomnia exhibit working memory deficits correlated with cognitive performance, alongside altered connectivity patterns between the prefrontal and temporal regions (28). These findings suggest that these regions may constitute the neural basis of cognitive impairment in this population. Furthermore, acupuncture has been shown to modulate network connectivity within the prefrontal and temporal lobes in insomnia patients (29). Therefore, in this study, we will select the prefrontal and temporal regions as the regions of interest (ROIs) for activation and functional connectivity analyses. Visual representations will be generated to facilitate intuitive presentation.

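### The 37 per group follows only from an undeclared one-sided 5% alpha; under a conventional two-sided t-test with 36 completers per arm, power is about 82%, not the stated 90%

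*Protocol article*

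**What the plan says.** Section 3.3 bases the sample size on MoCA change in a prior study: "The differences in MoCA scores before and after treatment was (3.22 ± 1.88) for the acupuncture group" and "1.97 ± 1.77) for the placebo acupuncture group". It sets alpha at 0.05, beta at 0.10 and k at 1, and reports that "a sample size of 37 cases per group was calculated". The printed formula multiplies (u_α + u_β)² by (1 + 1/k)σ²/δ². It writes u_α with no division of alpha by two, and the text does not say whether alpha is one-sided or two-sided. The section then continues: "Considering a dropout rate of 20%, we determined a sample size of 45 cases per group", which makes 90 in total.

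For the imaging subset, section 3.3 says "we will enroll at least 20 participants per group in fNIRS scanning" and raises this to 24 per group for the same 20% dropout.

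Section 7 plans an independent-samples t-test between groups (Mann–Whitney if the data are not normal), under ITT with LOCF. A p-value "of ≤0.05 will be considered statistically significant". It mentions no one-sided test or directional hypothesis. Allocation is 1:1 (section 3.10).

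**The concern.** A sample size and the test it serves should use the same alpha. If 37 was obtained by spending the whole 5% in one tail, while the analysis reports an ordinary two-sided p-value against 0.05, the beta of 0.10 in section 3.3 does not describe the trial that will be run. Someone reading a null MoCA result against a stated 90% power would give it more weight as evidence of no effect than the design supports.

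The dropout step raises a smaller question of the same kind: does the inflated number, after the assumed loss, still leave the number said to be needed?

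**Working it through.** **Inputs (section 3.3).** Difference δ = 3.22 − 1.97 = 1.25, so δ² = 1.5625. Pooled variance σ² = (1.88² + 1.77²)/2 = 3.334, so σ = 1.826. k = 1, so (1 + 1/k) = 2. α = 0.05, β = 0.10, u_β = 1.282.

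**Reproducing the plan's figure.** n = (u_α + u_β)² × 2 × 3.334/1.5625 = (u_α + u_β)² × 4.267.

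- One-sided 5%: (1.645 + 1.282)² × 4.267 = 36.54, so **37**. This is the plan's number.
- Two-sided 5%: (1.960 + 1.282)² × 4.267 = 44.84, so **45**. The exact t-test needs 46.

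The choice of SD does not rescue a two-sided reading at β = 0.10. With SD 1.88 alone the formula gives 47.5 two-sided and 38.7 one-sided; with SD 1.77 alone, 42.1 and 34.3. The 37 appears only one-sided, with the two SDs combined.

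**Dropout step.** 37 × 1.2 = 44.4, so 45, which is the plan's number. To have 37 left after a 20% loss requires 37/0.8 = 46.25, so 47. As planned, 45 × 0.8 = 36. For fNIRS, 20 × 1.2 = 24 is the plan's number, whereas 20/0.8 = 25; as planned, 24 × 0.8 = 19.2.

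**Power for 1.25 points, SD 1.826, noncentral t, α = 0.05.**

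| Analysed per arm | Two-sided | One-sided |
|---|---|---|
| 36 | 81.7% | 89.1% |
| 37 | 82.8% | 89.8% |
| 45 | 89.5% | 94.3% |
| 46 | 90.1% | 94.7% |

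**Which error matters.** At 37 per arm, moving from one-sided to two-sided costs 7.0 points (89.8% to 82.8%). Going from 37 to 36 completers costs a further 1.1 points (82.8% to 81.7%). Sidedness therefore accounts for almost all of the loss.

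**Detectable difference.** With 36 per arm and a two-sided test, 90% power is reached at a difference of 1.415, so about 1.42 points.

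**Range under ITT with LOCF.** Both ends are assumptions, since the article does not say when or why patients will leave.

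- Upper end: all 45 per arm are analysed and imputed values carry the full effect. Power is 89.5%.
- Lower end: the 20% who drop out carry baseline forward, so their change is zero. The expected difference becomes 0.8 × 1.25 = 1.00. The arm variances are 0.8 × 1.88² + 0.16 × 3.22² = 4.486 and 0.8 × 1.77² + 0.16 × 1.97² = 3.127, a pooled SD of 1.951. With 45 per arm, power is about 67%.

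**Two-sided 90% power after 20% dropout, for reference.** 45/0.8 = 56.25, so 57 per arm (114 in total). By the exact t-test, 46/0.8 = 57.5, so 58 per arm (116).

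**The case against.** *Two-sidedness is inferred.* This stands. Neither section 3.3 nor section 7 states it, and the formula, taken literally with u_α, returns 37 exactly. A reader might infer that the arithmetic is wrong or that the document commits itself to a two-sided test; it supports neither. The fault is an undeclared one-sided alpha beside a test that is two-sided unless stated otherwise. Section 3.3 needs correcting on either reading: declare and justify one-sided testing, or restate the power. An analysis plan that chose two-sided testing would not make 37 consistent with β = 0.10.

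*The 82% is not the power of the planned analysis.* This also stands. It counts completers, as the sample size section's own dropout allowance does, whereas section 7 analyses everyone randomised with LOCF. A reader might infer that a true 1.25-point effect would be missed 18% of the time; that is one point in a range from about 67% to 89.5%. Section 7 also applies a false discovery rate correction to clinical p-values, which none of these figures includes.

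*The dropout error is trivial.* Largely so for the main trial: one completer per arm, and one-sided power at 36 is still 89.1%. It should not be presented as a joint cause of the loss.

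*The fNIRS target is met literally.* Enrolling 24 does enrol at least 20. The shortfall exists only if 20 means evaluable scans, which the added dropout allowance suggests. The target rests on typical published group sizes of 10 to 25, so no power claim is affected.

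*The trial calls itself exploratory.* Section 9.1 does, and it defers a larger sample to later research. That softens the consequence, but section 3.3 still states β = 0.10 and does not disclose the discrepancy.

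**Conclusion.** The concern holds in this form: the stated 90% power is not delivered under the conventional reading of the planned test. On section 3.3's own terms (45 randomised, 20% lost, 36 completers per arm, difference 1.25, SD 1.826), two-sided power is about 82%, a type II error of about 18% against the stated 10%. This assumes a two-sided test, which is convention and not text, and completers only.

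The multiplied dropout allowance is a real but minor error: 36 remain against 37 needed, and about 19 against 20 for fNIRS if 20 means evaluable scans.

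Two further inferences should be resisted. The total of 94 (2 × 47) is not what the trial needs for two-sided 90% power; it applies only if a one-sided test is declared and justified. Nor can it be said that a baseline-adjusted analysis would recover most of the lost power, because that depends on a baseline-to-follow-up correlation that the article does not give.

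**What to change.** Keep 90 patients and revise section 3.3, with a matching statement in section 7:

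- State that the primary test is two-sided at 5%.
- Restate the power: 45 randomised and 36 expected completers per arm give about 82% for a 1.25-point difference, or 90% for about 1.42 points, conditional on completers.
- Write the dropout step as n/(1 − 0.20).
- For fNIRS, state about 19 expected evaluable scans per group, or scan 25 of the 45 already enrolled in each arm.

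The cost is rewording and a less favourable power statement, plus one more scanned participant per arm if that option is taken; no extra enrolment is needed. The alternatives cost more. Holding two-sided 90% power after 20% dropout takes 57 to 58 per arm (114 to 116 in total). Keeping the one-sided calculation requires declaring and justifying a one-sided test, with 47 per arm (94 in total).

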### Participants

3.4

This trial is aimed at aging individuals diagnosed as CID with MCI. Participants will be recruited from the clinical center. Eligible participants will be randomly divided into either an 8-week manual acupuncture or placebo acupuncture group.

### Recruitment and procedure

3.5

The recruitment will be conducted through advertisements and online platforms. Participants will be recruited from the Preventive Healthcare Center at the Affiliated Hospital of Chengdu University of Traditional Chinese Medicine. Recruitment efforts will involve posting posters in Preventive Healthcare Center and promotional content on the WeChat platform, outlining information such as the target patient population, eligibility criteria, interventions, and contact details. Participants will be provided study brochure and requested to fill up screening form. Patients will be required to sign a informed consent form if they meet the eligibility and agree to participate. Outcomes will be evaluated at baseline, 4 weeks (mid-intervention), 8 weeks (post-intervention), and follow-up period. In each group, 24 individuals will be selected for fNIRS scanning before and after intervention. Additionally, 24 healthy participants and 24 insomnia patients without cognitive impairment will be included as controls for assessing the brain functional characteristics of CID with MCI patients before intervention (Figure 1).

**Figure 1 fig1:**
[figure not shown]
The flowchart of trial procedures.

### Diagnostic criteria

3.6

The criteria for diagnosing CID are as follows: (1) meeting the diagnostic standards in the International Classification of Sleep Disorders (ICSD); (2) experiencing difficulty falling asleep, maintaining sleep, or waking up early on at least 3 nights per week for a duration of 3 months; and (3) an inability to attribute these sleep difficulties to other sleep disorders.

The criteria for diagnosing MCI are as follows: (1) the patient or a reliable informant reports cognitive impairment or a clinician with experience detects it; (2) impairment is observed in cognitive domains (memory, language, visuospatial, and executive functioning); (3) the patient can perform daily activities without assistance; and (4) dementia is not present.

### Eligibility criteria

3.7

Participants will be recruited if they meet the following criteria: (1) conform to the ICSD-3 diagnostic criteria for CID and Pittsburgh Sleep Quality Index (PSQI) score > 7; (2) cognitive impairment reported by the caregiver and confirmed by an experienced clinician; (3) impairment is observed in any aspect of memory, language, visuospatial, or executive functioning; (4) aged between 50 and 75 years, any gender, right-handed; (5) ongoing daily activities without assistance; (6) without dementia; (7) without recent acupuncture interventions (at least 1 month); (8) capable of effective communication and cooperation without severe visual or hearing impairment; and (9) willing to enroll and provide informed consent.

### Exclusion criteria

3.8

The exclusion criteria are as follows: (1) severe cardiovascular, cerebrovascular, hepatic, renal, infectious, malignant, or hematological diseases, as well as any severe conditions that could impact trial outcomes or increase participation risk; (2) cognitive dysfunction secondary to other conditions, such as coronary heart disease, chronic obstructive pulmonary disease, head trauma, stroke, etc.; (3) pregnancy or lactation; (4) allergies to metal or adhesive; (5) severe skin lesions at the needling site; (6) participation in other research projects; (7) inability to schedule suitable participation times or lack of sufficient willingness or confidence to complete the trial; and (8) previous receipt of acupuncture.

### Termination criteria

3.9

The termination criteria are as follows: (1) Severe safety issues arise; (2) The treatment is ineffective, lacking clinical value; (3) Significant errors in the clinical trial protocol or major deviations occur during implementation; (4) The project applicant requests termination (e.g., due to funding reasons, management reasons, etc.); and (5) Administrative authorities revoke the trial.

### Randomization and blinding

3.10

Participants will be randomly assigned to two groups in a 1:1 ratio using computer-generated random numbers. During intervention phase, participants will be administered separately in quiet treatment rooms to prevent interactions from different groups. Throughout the study, researchers, acupuncturist, efficacy assessors, and data statisticians will remain segregated. Only the acupuncturist aware of the group assignment result. Participants, evaluators, and analysts will be blinded to group assignments.

### Data monitoring committee

3.11

The Data Monitoring Committee (DMC) for this study comprised independent experts with no direct involvement in the research project. The committee included [name], who provided expertise in data analysis and statistical oversight, and [name], who contributed to evaluating safety and efficacy from an acupuncture perspective.

The DMC was responsible for monitoring safety and efficacy data, reviewing interim results, and making recommendations regarding the continuation, modification, or termination of the trial. The committee operated independently from both the research team and the ethics committee to ensure objective oversight.

## Intervention

4

Following the STRICTA guidelines (30), the treatment will focus on specific acupuncture points. The selection of these points was based on traditional Chinese medicine theory, supplemented by evidence from prior research findings, including systematic reviews and meta-analyses, data mining results (36–38), and the consensus of experienced experts within our research team. The selected acupoints include Baihui (GV20), Sishencong (EX-HN1), Shenting (GV24), Shenmen (HT7), Xuanzhong (GB39), and Dazhong (KI4).

The localization and manipulation of acupoints rooted in Traditional Chinese Medicine (TCM) standards (Figure 2). To ensure blinding, the Park Sham Device (PSD) will be utilized following skin disinfection. Adhesive tape will secure acupoints on extremities, while a hair gripper will be used for acupoints on the head (Figures 3, 4). Patients could receive basic supportive care or sleeping pill. Detailed such as duration, dose, frequency, and response will be recorded.

**Figure 2 fig2:**
[figure not shown]
Localization of the applied acupoints. GV20: located at the highest point on the head, in the midline, directly on the apex of the head. EX-HN1: situated around GV20, with one point in each of the four directions: anterior, posterior, left, and right. These points are typically located about 1 cun (Chinese inch) away from GV20 in each direction. GV24: located on the Du Meridian, at a point 0.5 cun directly above the midpoint of the anterior hairline. HT7: located on the transverse crease of the wrist, on the ulnar aspect of the palm, in the depression between the tendons of the flexor carpi ulnaris and the flexor digitorum superficialis. GB39: located on the lateral side of the lower leg, about 3 cun above the external malleolus, near the anterior border of the fibula. KI4: located on the medial side of the foot, posteroinferior to the medial malleolus, at the upper edge of the calcaneus, in the depression at the anterior attachment of the achilles tendon.

**Figure 3 fig3:**
[figure not shown]
The device of manual or placebo acupuncture.

**Figure 4 fig4:**
[figure not shown]
The specialized device of manual or placebo acupuncture for areas covered by hair.

### Manual acupuncture group

4.1

Participants in the manual acupuncture group will receive intervention with PSD + disposable sterile needles (Hwato, Suzhou, China; 0.25 × 25 mm). After disinfection, the PSD will be placed at the acupoints, disposable sterile needles will be quickly inserted into the skin using a pre-prepared tube. For acupoints on the head, including Baihui (GV20), Sishencong (EX-HN1), and Shenting (GV24), needles are inserted at a 15° angle to a depth of 0.5 cun (approximately 13 mm). For other acupoints, including Shenmen (HT7), Xuanzhong (GB39), and Dazhong (KI4), needles are inserted perpendicularly at a 90° angle to a depth of 1 cun (approximately 25 mm).

The practitioner will perform lifting, thrusting, or rotating techniques to elicit the “deqi” sensation, which indicates the therapeutic efficacy of acupuncture. “De qi” typically manifests as sensations of soreness, numbness, fullness, or radiance and helps practitioners confirm whether the needling technique is appropriate, ensuring treatment accuracy. Due to individual differences among participants, acupuncturists adjust their techniques based on each participant’s specific condition to achieve “deqi” sensation. The needles will then be retained for 30 min.

### Placebo acupuncture group

4.2

Participants in the placebo acupuncture group will receive intervention with PSD + retractable blunt needles (AcuPrime; 0.25 mm × 25 mm). After placing the device, retractable blunt needles will be used to simulate needle insertion, creating the sensation of being stimulated by a needle without actually penetrating the skin. No lifting, thrusting, or rotating techniques will be performed to avoid generating the sensation of Deqi, and the needles will be retained for 30 min.

## Outcome measures

5

Each participant will be evaluated by a medical professional blinded to the group assignment and intervention. Assessments will occur at five time points: baseline, 4 weeks, 8 weeks, 12 weeks, and 20 weeks. The schedule of this study is listed in Table 3.

**Table 3 tab3:** Study schedule.

Timepoint	Enrolment	Baseline	Treatment phase		Follow-up phase	
	1 week	0 week	4 weeks	8 weeks	1 month	3 months
Enrolment						
Eligibility screen	**×**					
Medical history	**×**					
Informed consent		**×**				
Allocation		**×**				
Interventions						
Manual acupuncture		**×**	**×**	**×**		
Placebo acupuncture		**×**	**×**	**×**		
Health education		**×**	**×**	**×**		
Assessments						
Demographics	**×**					
fNIRS scanning		**×**		**×**		
PSQI	**×**	**×**				
MoCA	**×**	**×**	**×**	**×**	**×**	**×**
ISI		**×**	**×**	**×**	**×**	**×**
MMSE		**×**	**×**	**×**	**×**	**×**
PHQ-7		**×**	**×**	**×**	**×**	**×**
GAD		**×**	**×**	**×**	**×**	**×**
AES		**×**	**×**	**×**	**×**	**×**
SF-12		**×**	**×**	**×**	**×**	**×**
Safety assessment		**×**	**×**	**×**		
Vital sign		**×**	**×**	**×**		
Use of sleep medications		**×**	**×**	**×**	**×**	**×**

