**Methods and design:**

This study is a single-center randomized controlled trial. Participants will be randomly assigned to the manual acupuncture group or the placebo acupuncture group for an 8-week intervention period. fNIRS data will be collected during resting test and working memory test at baseline and at end of the intervention. The primary outcome is the change of the Montreal Cognitive Assessment (MoCA) score, secondary outcomes include the change of Mini-Mental State Examination (MMSE), Insomnia Severity Index (ISI), Patient Health Questionnaire-9 (PHQ-9), Generalized Anxiety Disorder Scale (GAD-7), and Apathy Evaluation Scale-Informant (AES-I).

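### MoCA is scheduled twice before treatment, but on the natural reading only the week-0 score enters the primary comparison; using both would sharpen it at almost no cost

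*Protocol article*

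**What the plan says.** The abstract (Methods and design) states: "The primary outcome is the change of the Montreal Cognitive Assessment (MoCA) score". It does not say which pre-treatment score is the reference.

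Section 5 states: "Assessments will occur at five time points: baseline, 4 weeks, 8 weeks, 12 weeks, and 20 weeks". Table 3, directly below, marks MoCA in six columns: enrolment (labelled 1 week), baseline (0 week), weeks 4 and 8, and two follow-up visits. The sixth sitting, at enrolment, is not in the sentence. PSQI is likewise marked at enrolment and at week 0, and informed consent is marked at week 0.

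Section 7 fixes the test for normally distributed data: "comparisons between groups will be made using an independent samples *t*-test". It also plans paired tests within each group, an intention-to-treat analysis and last observation carried forward. It names no covariates.

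Section 3.3 bases the sample size on change in MoCA: "The differences in MoCA scores before and after treatment was (3.22 ± 1.88) for the acupuncture group", against 1.97 ± 1.77 under placebo.

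**The concern.** A change score carries the measurement error of both sittings from which it is formed. If only week 0 serves as the reference, the full error of one pre-treatment MoCA enters every participant's change, although the schedule provides a second reading shortly before it. Both readings precede treatment, so using both cannot bias the randomised contrast.

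The point does not depend on whether the test is a t-test or a covariate-adjusted model, because the enrolment score adds information to either. At stake is the precision of the primary comparison in a trial of 90 participants. Section 9.1 itself looks to a larger sample in future research for more power.

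**Working it through.** **Inputs from section 3.3.** Difference 3.22 − 1.97 = 1.25. Pooled variance (1.88² + 1.77²)/2 = 3.334, so pooled SD 1.826. Power 90%, α 0.05 with sidedness not stated, 37 per group, 45 after the dropout allowance.

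**The plan's own figure.** n = (u_α + u_β)² × 2σ²/δ².
- One-sided: (1.645 + 1.282)² × 2 × 3.334/1.5625 = 36.5, so 37, as stated.
- Two-sided: (1.960 + 1.282)² × 2 × 3.334/1.5625 = 44.8, so 45.

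The stated figure is therefore reproduced only one-sided. That is a separate sample-size matter; here it only shows that the power figures below depend on sidedness.

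**Change in variance.** Let r be the correlation of the two pre-treatment scores and ρ the pre–post correlation, with equal variances s².
- One pre-treatment score: 2s²(1 − ρ).
- Mean of two: s²(1.5 + r/2 − 2ρ).
- Relative cut: (1 − r)/(4(1 − ρ)).

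This is 25% whenever r = ρ and smaller when r exceeds ρ: 12.5% at r 0.90, ρ 0.80; 8.3% at 0.90, 0.70; 5% at 0.90, 0.50.

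**Tied to the protocol's variance.** Let e be the measurement-error SD of one sitting (assumed, independent between sittings) and d² the variance of true individual change. One score gives d² + 2e² = 3.334; the mean of two gives d² + 1.5e². The cut is (e²/2)/3.334. Since 2e² cannot exceed 3.334, e is at most 1.29.

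The covariate column uses residual variance d² + e² + T²e²/(T² + e²) with one score, replacing e² by e²/2 in the last term with two. T is the SD of true scores between persons, assumed to be 3. Power is for a two-sided 5% t-test on the change, with SD 1.826 × √(1 − cut).

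| e (assumed) | cut, change score | cut beyond covariate model on week 0 | power, 36 per arm | power, 45 per arm |
|---|---|---|---|---|
| week 0 only | – | – | 81.7% | 89.5% |
| 0.5 | 3.7% | 3.6% | 83.1% | 90.5% |
| 1.0 | 15.0% | 13.2% | 87.4% | 93.6% |
| 1.29 | 25.0% | 20.9% | 91.1% | 96.0% |

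Thirty-six is 45 × 0.8, the completers if the allowed 20% drop out.

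**If entry is restricted on the enrolment score.** Simulating selection to MoCA 18–25 moves the change-score cut at e = 1.29 from 25% to about 26%. It lowers the gain beyond the covariate model to about 16% (e = 1.29, T = 3). With T = 2 and no selection, that gain is 3.4% to 17.1% over the same range of e.

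**The case against.** The strongest objection is that the article never says the enrolment score is set aside. It does not define how baseline is derived, and that is commonly left to the analysis plan. The enrolment column holds the eligibility screen, and PSQI, an entry criterion, has the same two marks, so the first MoCA looks like a screening score. A week-0 reference is standard and unbiased. This stands: no error is shown, and a reader who infers that the plan explicitly discards the score goes further than the text. What remains is that the five-visit sentence and the unadjusted test, read together, give the enrolment score no role.

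A reader might also infer a fixed gain of 13–26%. The document gives no retest correlation, error SD or cross-sectional SD, and lower measurement error gives a gain of only about 4%. An entry limit of 18–25 is also not among the criteria in section 3.7; section 5.1.1 gives that range only as an interpretation of the score.

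A third tempting inference is that the trial is underpowered and the second score repairs it. The 82% assumes a two-sided test and 36 completers. Under intention to treat with last observation carried forward, nominally 45 per arm are analysed, which gives 89.5%. Carried-forward values may dilute the difference, so neither count is exact. Any shortfall belongs to the sample-size section.

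Finally, the gain is not wholly free. Averaging in the enrolment score shifts each arm's own change by half of any practice gain, and by any regression to the mean if that score is used for selection. Both affect the arms equally and leave the between-group contrast alone, but they would alter the planned within-group paired tests. Consent is marked after the enrolment MoCA.

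**Conclusion.** The point holds as an efficiency improvement. Two pre-treatment MoCA scores are scheduled, and on the natural reading one is unused in the primary comparison. Using both lowers the variance in every scenario tried: by about 4–26% for the change score and, at most, about 4–21% beyond a covariate model on week 0 alone, for an assumed error SD of 0.5 to about 1.3 points. In two-sided power that is 82% to 83–91% at 36 per arm, or about 90% to 91–96% at 45.

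These ranges rest on independent errors of equal size at each sitting, on true change unrelated to the pre-treatment level, and on the protocol's own difference and SDs. The lower end is a small gain. The documents support neither a claim of bias nor a claim that the plan is wrong to use week 0.

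**What to change.** Add to section 7 that the between-group MoCA comparison uses both the enrolment and the week-0 score. Entering them as separate covariates is preferable: with week 0 among the covariates, the group effect is the same whether the outcome is the later score or the change from week 0, so the stated primary outcome can stay. If an unadjusted change score is kept, take the change from the mean of the two. Keep week 0 alone as a sensitivity analysis and as the reference for the within-group paired tests. Fix this before unblinding.

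The cost is a sentence or two, with no added visit or participant. The sponsor should confirm that the consent marked at week 0 covers use of the enrolment score as outcome data.
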